### Sample size

The sample size estimate was based on the RCT of the same dose and preparation of EPA-FFA in FAP patients [15], a meta-analysis of aspirin RCTs [22] and detailed 2007–2008 BCSP audit data from the South of Tyne and Tees BCSP Centres.

In order to detect a minimum 18% relative reduction in adenoma risk in each two-arm comparison (less than the 22% reduction in polyp number compared with placebo in the FAP Trial [15] and below the absolute reduction in polyp number at one year [38%] in the aspirin RCTs [22]) from a 60% adenoma recurrence rate (South of Tyne and Tees BCSP data) at surveillance colonoscopy to 49%, 678 evaluable ‘high risk’ individuals need to be randomized equally to the four treatment arms, with 80% power at a 5% two-sided significance level. Standard practice for 2 × 2 factorial designs in the assumed absence of any interaction bases the sample size estimate on comparison ‘at the margins’ of active treatment A vs. placebo A (half of whom in each arm receive active treatment B and the other half placebo B). Assuming the same target effect size and alpha, this yields the same power for the marginal comparison of active treatment B vs. placebo B (half of whom in each arm receive active treatment A and the other half placebo A). With a total sample size of 678 for analysis, there is, in fact, a slight reduction in power (to 75%) which arises if *both* treatments work, because then the overall comparison for treatment A is not 0.49 vs. 0.6, but is 0.445 vs. 0.545 (averaging over the placebo and treatment B arms). To keep power at 80% for the above figures, 192 individuals are required per arm (total 768 evaluable ‘high risk’ individuals). Allowing for a 15% drop-out rate increases the sample size to 768/0.85 = 904 individuals.

Data from the South of Tyne and Tees BCSP Centres indicated that 20% of ‘high risk’ patients were expected to be using aspirin, and thus be ineligible for the trial. An allowance was made for an additional 20% of ‘high risk’ patients to be ineligible due to other reasons. Based on the assumption that 40% of patients would be ineligible it was calculated that a total of 904/0.6 = 1,507 ‘high risk’ patients would need to be identified at BCSP screening colonoscopy. Trial timelines were based on BCSP data suggesting that a BCSP Centre identifies approximately 50 ‘high risk’ patients per year. On this basis, the Trial intervention period was predicted to be 2 years and require 15 BCSP Centres (approximately 30 BCSP endoscopy sites).

### Statistical analysis

The main approach to analyses will be intention-to-treat (ITT), where the ITT population consists of all randomised participants. No adjustment for multiple significance testing was made in the sample size estimate or will be in the analyses. Results of comparative analyses will be presented as the appropriate point estimate (for example, risk ratio or difference in means), 95% confidence interval and *P* value. No formal interim analysis for efficacy is planned and hence there are no ‘stopping rules’.

#### Descriptive analyses

The baseline comparability of the groups will be assessed with regard to the following variables: age at randomization, gender, body mass index, cigarette smoking, alcohol consumption, diagnosis of diabetes, requirement for a repeat colorectal endoscopic procedure within 3 months, number of adenomas detected at baseline, number of ‘advanced’ adenomas detected at baseline and the location of adenomas in the colorectum. Categorical (including binary) variables will be summarized by reporting numbers and percentages in each category, continuous variables will be summarized using means and standard deviations. Missing data will be tabulated.

#### Primary analyses

For the primary outcome, it is anticipated that the 2 × 2 factorial trial will be analysed by an ‘at the margins’ approach, after first examining whether there is any evidence of an interaction between EPA and aspirin [29], although it is recognized that this will lack power to detect anything but a very large interaction effect. The log relative risk will be estimated using a log-binomial regression model with robust standard errors to allow for potential non-independence of observations within a BCSP centre. Both interventions will be fitted simultaneously and in a further secondary analysis, adjusted for ‘repeat colorectal endoscopic procedure within 3 months required’ plus any other covariates identified as important from the baseline comparisons. Should there be strong evidence of an interaction between EPA and aspirin, the effect of each treatment alone will be examined using an ‘inside the table’ approach, although it is recognized that precision for these analyses may be reduced since each uses only approximately 50% of the available sample.

A per-protocol analysis will be conducted as a sensitivity analysis, where the per-protocol population consists of all randomized participants who were not deemed to have a protocol violation. Additionally, some BCSP centres consist of multiple hospitals (sites), therefore an additional sensitivity analysis will be conducted in which both BCSP centre and site will be treated as random effects in a multi-level model.

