#### Secondary analyses

All secondary end-points will be analysed using the ITT population, with the exception of adverse events, for which we will analyse the safety population, consisting of all participants who received at least one dose of trial medication.

• The relative recurrence of ‘advanced’ adenoma detected at the first BCSP surveillance colonoscopy will be analysed using a log-binomial regression model with robust standard errors to estimate the log relative risk.

• Number of ‘advanced’ adenomas per participant at the first BCSP surveillance colonoscopy will be analysed using a Poisson regression model with robust standard errors.

• Number of adenomas per participant at the first BCSP surveillance colonoscopy will be analysed using a Poisson regression model.

• The region of the colorectum where adenomas are detected at the first BCSP surveillance colonoscopy will be explored, possibly using a Poisson random effects model with bivariate response (corresponding to polyp counts in the left and right colon) in which treatment and a baseline polyp count will be independent variables together with random intercepts corresponding to patient and BCSP Centre.

• The number of ‘high risk’ participants re-classified as ‘intermediate risk’ after the first BCSP surveillance colonoscopy will be analysed using binary regression or logistic regression, treating centre as a random effect.

• The number of participants with CRC detected prior to or at the first BCSP surveillance will be analysed descriptively, and possibly using a logistic regression model depending on numbers with this outcome, although it is anticipated that there will be low power due to small numbers.

Adverse events, including clinically significant bleeding episodes will be summarized by tabulating the number (and percentage) of events occurring in each treatment arm. All participants who receive at least one dose of treatment will be included in the safety analysis. Mis-randomised participants will be analysed as treated. Adverse drug reactions (ADRs) will be summarized by severity using the preferred term and the worst severity and causality recorded. The worst case will be assumed if severity or causality are missing. All participants who experience treatment-emergent ADRs will be listed including participant identification, treatment arm, system organ class, preferred term, unexpectedness, seriousness, severity, start and stop dates/times, action taken and outcome.

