## Discussion

The first patient first visit (FPFV) of the Trial was 11th November 2011. It soon became clear from screening logs at individual BCSP sites that the eligibility rate was 15–20% rather than the 60% that had been predicted in the original sample size calculation. One contributing factor was the use of other non-aspirin anti-platelet agents such as clopidogrel, which we later added as an extra exclusion criterion (Protocol version 3.1 dated 12 Jan 2012), in order to completely rule out the possibility of excess bleeding risk due to concomitant use of three agents with anti-platelet activity in one arm of the Trial. Another major contributing factor was the larger than expected number of ‘high risk’ individuals (approximately 25%) who required a repeat endoscopy, which was an exclusion criterion in earlier versions of the Trial protocol. We obtained data on the proportion of ‘high risk’ patients undergoing a repeat endoscopic procedure from participating BCSP sites and demonstrated that there had been a consistent increase in the number of patients undergoing repeat ‘re-look’ procedures since the start of the BCSP in 2006 and that ‘re-look’ rates varied significantly across BCSP sites. ‘High risk’ patients, who require a repeat screening procedure, were originally excluded from the Trial on the basis that the primary end-point might be confounded by adenoma detection and removal at an extra endoscopic procedure in-between the screening and one-year surveillance procedures. However, subsequent analysis (in April 2012) of the North-East BCSP Hub (9 BCSP Centres) and the Southern BCSP Hub (17 BCSP Centres) data on ‘high risk’ patients who underwent one-year surveillance colonoscopy in 2010 did not support this notion. Of 1,189 ‘high risk’ patients, 930 (78%) went straight to one-year surveillance after a single screening colonoscopy. One or more adenomas were detected in 465 (63%) of 738 patients, for whom data were available. The corresponding adenoma detection rate for ‘high risk’ patients, who underwent a repeat partial colonoscopy or flexible sigmoidoscopy within 3 months of the initial screening colonoscopy was 54% (59/110), but the adenoma detection rate in patients who underwent a repeat full colonoscopy was 67% (56/83). The overall adenoma detection rate at first surveillance colonoscopy was 62%, which is consistent with the value (60%) used in our original sample size calculation, although the cohort included patients who had undergone a repeat screening endoscopy. Therefore, we amended the protocol in order to allow recruitment of those individuals who require no more than one repeat endoscopic procedure (either colonoscopy or flexible sigmoidoscopy) within the 3-month screening episode window (Protocol version 4.0 dated 24 May 2012).

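### The secondary adjusted analysis of the primary end-point picks its covariates from observed baseline comparisons, with no criterion, instead of naming prognostic ones in advance

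*Protocol article*

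**What the plan says.** Under Primary analyses, the primary end-point (one or more adenomas at the first surveillance colonoscopy) is analysed by log-binomial regression with robust standard errors. The order is explicit: "Both interventions will be fitted simultaneously and in a further secondary analysis, adjusted for" the need for a repeat colorectal endoscopic procedure within three months, "plus any other covariates identified as important from the baseline comparisons". The main model therefore holds EPA and aspirin only, and the covariates belong to a secondary analysis.

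Descriptive analyses defines the baseline comparisons. It lists ten variables on which group comparability is assessed, among them "requirement for a repeat colorectal endoscopic procedure within 3 months, number of adenomas detected at baseline", the number of advanced adenomas and their location. Nothing says how a variable comes to be judged important.

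Under Secondary analyses, a possible model for adenoma location is described "in which treatment and a baseline polyp count will be independent variables". The Discussion gives one-year audit results by type of repeat procedure. For patients with a single screening colonoscopy: "One or more adenomas were detected in 465 (63%) of 738 patients, for whom data were available". The rate was 54% (59/110) after a repeat partial colonoscopy or flexible sigmoidoscopy, and 67% (56/83) after a repeat full colonoscopy.

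**The concern.** This is a stated rule, not a detail left to an analysis plan, and a plan that follows it inherits the problem. In a randomised trial a baseline difference between arms is a chance event. It says nothing about whether the variable predicts the outcome, which is the reason to adjust. Selection by imbalance can bring in variables of no prognostic value and leave out prognostic ones that happen to be balanced. Without a criterion, two analysts with the same baseline table could fit different adjusted models, and that result will be reported beside the main one.

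Baseline adenoma count is the clearest candidate at risk of omission. Eligibility is itself defined by adenoma number and size, and the count is known before randomisation. For the primary end-point it nevertheless enters only if the arms happen to differ on it.

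**Working it through.** 1. **The plan's own figures.** Inputs from Sample size: 60% vs 49%, two-sided 5%, 80% power, 678 evaluable (339 per margin); if both treatments work, 54.5% vs 44.5% and 768 evaluable (384 per margin). With the usual two-proportion formula, 60% vs 49% needs 321 per margin, or 339 with continuity correction, so 678 is reproduced. For 54.5% vs 44.5% without correction it gives 392 per margin, 784 in total, within 2.1% of 768. Power at 678 is 74.1% (stated 75%). Power at 384 per margin:

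   z = [0.10 × √384 − 1.96 × √(2 × 0.495 × 0.505)] / √(0.545 × 0.455 + 0.445 × 0.555) = (1.9596 − 1.3858) / 0.7035 = 0.816, so power is 79.3%. This is the baseline below.

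2. **How often the rule could be triggered by chance.** Ten variables are listed and one (repeat procedure) is already fixed, leaving nine. If importance meant P<0.05 and the variables were independent (both assumptions), the chance that at least one is flagged is 1 − 0.95^9 = 37% for one margin and 1 − 0.95^18 = 60% over both. Total and advanced adenoma counts are probably correlated, so these are rough figures.

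3. **Effect on error and power.** Simulation on a linear-probability scale: 768 patients, ten covariates, a prognostic covariate explaining about 1%, 4% or 9% of outcome variance, 3,000 runs per setting. The Monte Carlo standard error is √(0.05 × 0.95 / 3000) = 0.4 points for type I error and √(0.8 × 0.2 / 3000) = 0.7 points for power.

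| Variance explained | Type I: unadjusted | Type I: chosen by imbalance | Type I: most favourable model | Power: unadjusted | Power: chosen by imbalance | Power: pre-specified |
|---|---|---|---|---|---|---|
| 1% | 5.3% | 5.0% | 7.0% | 79.0% | 79.3% | 80.2% |
| 4% | 5.0% | 5.2% | 7.2% | 79.8% | 80.2% | 82.3% |
| 9% | 4.3% | 4.3% | 6.6% | 79.2% | 80.0% | 83.5% |

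   Choosing by imbalance does not inflate type I error, but it recovers little of the available precision. Error rises, to about 7%, only when the most favourable of several adjusted models may be picked.

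4. **Precision by formula.** Effective N = 768 / (1 − R²), as an approximation. R² of 1%, 2%, 5% and 10% gives 776, 784, 808 and 853 patients, and power of 79.7%, 80.1%, 81.3% and 83.3%. For 10%: 384 / 0.9 = 426.7 per margin and z = (0.10 × √426.7 − 1.3858) / 0.7035 = 0.966. The R² values are assumptions; the article gives no prognostic strength for adenoma count.

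5. **The fixed repeat-procedure term.** From the Discussion:

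| Comparison | Rates | Difference in points (95% CI) | P |
|---|---|---|---|
| Partial or sigmoidoscopy vs none | 53.6% vs 63.0% | −9.4 (−19.3 to +0.6) | 0.059 |
| Full vs none | 67.5% vs 63.0% | +4.5 (−6.2 to +15.1) | 0.42 |
| Full vs partial or sigmoidoscopy | 67.5% vs 53.6% | +13.8 (0.1 to 27.6) | 0.053 |
| Any repeat (115/193) vs none | 59.6% vs 63.0% | −3.4 (−11.2 to +4.3) | 0.38 |

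   The three-group chi-square is 4.617 on 2 df, P=0.099. Variance explained by three levels is 4.617 / 931 = 0.50%, against 0.08% for yes/no. Three-level coding would move power from 79.3% to 79.5%.

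**The case against.** The strongest reply is that little depends on this rule. The main model contains the two treatments only, so its estimate, interval and P value cannot move with covariate choice, and a treatments-only primary analysis is valid. That stands. A reader might infer that the primary result is data-driven or its type I error inflated; the documents do not support this. The article does not describe picking the most favourable adjustment. It only fails to rule that out.

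A reader might also infer that the yes/no repeat term merges two groups of opposite risk. The point estimates lie on either side of the no-repeat rate, but no contrast reaches 5%. The data are also incomplete: 738 of 930 single-colonoscopy patients, and 193 of the other 1,189 − 930 = 259. There is a structural reason to separate the types: Trial schedule says that only a second full colonoscopy extends treatment beyond 12 months. However, the planned covariate is a repeat that is required, whereas the audit groups are defined by the procedure undergone. Eligibility is assessed about 7–14 days after screening and the repeat may fall anywhere in a three-month window, so its type may be settled only after randomisation. The documents do not show otherwise.

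Third, precision from adenoma count is not necessarily lost. The count is on the baseline list and could be selected, and the entry criteria restrict its range. Nor does the location model commit the plan to adjusting for count, since that model is offered only as a possibility. Both points stand, so the loss is possible, not shown.

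Finally, an analysis plan not seen here may already name the covariates. If so, the protocol's wording still needs to match it.

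**Conclusion.** The concern holds for the secondary adjusted analysis only. Its covariates, apart from the repeat-procedure term, are left to chance imbalance with no criterion. That analysis cannot be reproduced from the stated rule, and it may omit balanced prognostic variables. The main analysis is sound, and selection by imbalance does not by itself inflate type I error.

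The gain from fixing the covariates is about 0.4 to 4 points of power at 768 (79.3% to 79.7–83.3%), and it rests on an assumed 1–10% of outcome variance explained. The audit rates of 63%, 54% and 67% suggest but do not establish a difference by type of repeat. Making the adjusted model primary would be the sponsor's choice, not the correction of an error.

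**What to change.** Delete the clause that selects covariates from the baseline comparisons. Before unblinding, name the covariates of the adjusted model on prognostic grounds, to be fitted whatever the observed balance: number of adenomas at the entry colonoscopy, age, sex, and whether a repeat procedure was required. Keep the baseline table as description only. Split the repeat term into none, partial or sigmoidoscopy, and full colonoscopy only if the type required is recorded before randomisation; otherwise keep it as yes/no. The treatments-only model may stay primary.

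The cost is wording. Adenoma count, age, sex and the repeat requirement are already baseline items, and the sample size is unchanged; the one thing to check is when the type of repeat is recorded. The small downside is that a log-binomial model with continuous covariates may fail to converge at expected rates of about 45–60%. Name a fallback now, such as Poisson regression with robust standard errors, so that this choice too is not made after seeing the data.

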#### Secondary analyses

All secondary end-points will be analysed using the ITT population, with the exception of adverse events, for which we will analyse the safety population, consisting of all participants who received at least one dose of trial medication.

• The relative recurrence of ‘advanced’ adenoma detected at the first BCSP surveillance colonoscopy will be analysed using a log-binomial regression model with robust standard errors to estimate the log relative risk.

• Number of ‘advanced’ adenomas per participant at the first BCSP surveillance colonoscopy will be analysed using a Poisson regression model with robust standard errors.

• Number of adenomas per participant at the first BCSP surveillance colonoscopy will be analysed using a Poisson regression model.

• The region of the colorectum where adenomas are detected at the first BCSP surveillance colonoscopy will be explored, possibly using a Poisson random effects model with bivariate response (corresponding to polyp counts in the left and right colon) in which treatment and a baseline polyp count will be independent variables together with random intercepts corresponding to patient and BCSP Centre.

• The number of ‘high risk’ participants re-classified as ‘intermediate risk’ after the first BCSP surveillance colonoscopy will be analysed using binary regression or logistic regression, treating centre as a random effect.

• The number of participants with CRC detected prior to or at the first BCSP surveillance will be analysed descriptively, and possibly using a logistic regression model depending on numbers with this outcome, although it is anticipated that there will be low power due to small numbers.

Adverse events, including clinically significant bleeding episodes will be summarized by tabulating the number (and percentage) of events occurring in each treatment arm. All participants who receive at least one dose of treatment will be included in the safety analysis. Mis-randomised participants will be analysed as treated. Adverse drug reactions (ADRs) will be summarized by severity using the preferred term and the worst severity and causality recorded. The worst case will be assumed if severity or causality are missing. All participants who experience treatment-emergent ADRs will be listed including participant identification, treatment arm, system organ class, preferred term, unexpectedness, seriousness, severity, start and stop dates/times, action taken and outcome.

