#### Secondary end-points

i. The number of participants with one or more ‘advanced’ (≥10 mm diameter, high-grade dysplasia or tubulo-villous/villous histology) adenomas at the first BCSP surveillance colonoscopy.

ii. The number of ‘advanced’ adenomas per participant at the first BCSP surveillance colonoscopy.

iii. The total number of adenomas per participant at BCSP surveillance colonoscopy at the first BCSP surveillance colonoscopy.

iv. The region of the colorectum (right colon – any part of the colon proximal to the splenic flexure; left colon – the rectum and the colon distal to the splenic flexure) where adenomas are detected at the first BCSP surveillance colonoscopy.

v. The number of ‘high risk’ participants re-classified as ‘intermediate risk’ after the first BCSP surveillance colonoscopy (BCSP risk stratification at the first surveillance colonoscopy follows BSG Guidelines [23] so that any individual that does not continue to fulfil ‘high risk’ criteria is classified as ‘intermediate risk’ for further colonoscopic surveillance at three years).

vi. The number of participants with CRC detected prior to, or at, the first BCSP surveillance.

vii.  Adverse events, including clinically significant bleeding episodes.

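### Total adenoma count is assigned plain Poisson regression while the adjacent 'advanced' count gets robust standard errors; if counts are over-dispersed, its intervals and P values would be too optimistic

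*Protocol article*

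**What the plan says.** Secondary end-point iii in the protocol article is "The total number of adenomas per participant at BCSP surveillance colonoscopy". The Secondary analyses section assigns its model in one sentence: "Number of adenomas per participant at the first BCSP surveillance colonoscopy will be analysed using a Poisson regression model". Nothing is added about the variance estimator, dispersion or clustering.

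The neighbouring entries differ:

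- The bullet before it, for the count of 'advanced' lesions, reads "adenomas per participant at the first BCSP surveillance colonoscopy will be analysed using a Poisson regression model with robust standard errors".
- The bullet after it, for left and right colon counts, suggests a Poisson model with "random intercepts corresponding to patient and BCSP Centre", though only as a possibility to be explored.
- The binary 'advanced' adenoma outcome gets a log-binomial model with robust errors, and risk re-classification gets a centre random effect.
- The primary outcome is modelled "with robust standard errors to allow for potential non-independence of observations within a BCSP centre".

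The Statistical analysis section says that comparative results will carry a point estimate, "95% confidence interval and" P value, with no adjustment for multiple testing.

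**The concern.** Two adjacent count end-points, measured on the same people at the same colonoscopy, have different stated methods, and the article does not say why. Followed literally, the bullet for the total count yields model-based standard errors, which are valid only if the variance equals the mean.

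That is a demanding condition here. Participants enter because they had at least five small adenomas, or at least three with one of 10 mm or more. It is plausible that such people differ in how readily they form adenomas, and that some lesions at one year were missed at baseline in some patients more than in others. Variation of this kind pushes the variance above the mean. The estimated rate ratio would still be sound, but its interval would be too narrow and its P value too small. Because the result is to be reported with an unadjusted P value, no other part of the stated plan would correct for this.

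**Working it through.** **Inputs from the article**

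- Proportion with at least one adenoma at surveillance: 60% (Sample size) and 62% (Discussion). The second figure reproduces from the Discussion's counts: (465 + 59 + 56)/(738 + 110 + 83) = 580/931 = 62.3%.
- Evaluable participants: 192 per arm, so 2 × 192 = 384 on each side of a marginal comparison.
- Two-sided 5% level.

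**Input not in the article (assumed)**

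The mean and variance of the count are not given. I hold the zero proportion at 0.40 and let the mean run from the pure Poisson value up to 2.0 under a negative binomial distribution. The bullet itself carries no figure to reproduce.

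**Step 1: the mean at which plain Poisson is correct.** From P(0) = exp(−m), m = −ln(0.40) = 0.92, or −ln(0.38) = 0.97 at the 62% rate.

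**Step 2: dispersion at higher means.** For a negative binomial, P(0) = (k/(k + m))^k and variance/mean = 1 + m/k. Example: m = 1.5 with k = 1 gives P(0) = 1/2.5 = 0.40 and variance/mean = 1 + 1.5 = 2.5.

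**Step 3: effect on the test.** Poisson standard errors are too small by a factor √(variance/mean). The true size of the nominal 5% test is 2[1 − Φ(1.96/√(variance/mean))]. Example: 1.96/√2.5 = 1.24, giving 0.215.

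**Step 4: results with P(0) = 0.40**, with a simulation check (384 per side, 10,000 replicates, no treatment effect):

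| Mean | k | Variance/mean | SE too small by | Size, formula | Size, simulated | Size with robust SE | Coverage of 95% CI |
|---|---|---|---|---|---|---|---|
| 0.92 | Poisson | 1.00 | 1.00 | 5.0% | 4.8% | 4.9% | 95% |
| 1.0 | 5.32 | 1.19 | 1.09 | 7.2% | 6.8% | 4.9% | 93% |
| 1.2 | 1.77 | 1.68 | 1.30 | 13.0% | 13.6% | 5.1% | 87% |
| 1.5 | 1.00 | 2.50 | 1.58 | 21.5% | 21.4% | 5.1% | 79% |
| 2.0 | 0.65 | 4.06 | 2.01 | 33.0% | 32.8% | 5.2% | 67% |

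At the 62% rate, P(0) = 0.38, the formula gives slightly smaller sizes: 11.1%, 19.4% and 30.9% at means 1.2, 1.5 and 2.0. Robust errors there give 4.9–5.4%.

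**Step 5: what the article's own data show about heterogeneity.** The three Discussion subgroups (no repeat procedure 63%, repeat partial examination 54%, repeat full colonoscopy 67%) convert by −ln(1 − p) to Poisson means of 0.99, 0.77 and 1.12. Weighted by numbers, the overall mean is 0.979 and the between-group variance 0.0073, so variance/mean = 1 + 0.0073/0.979 ≈ 1.01. This one source of heterogeneity would do almost no harm. The article has no data on other sources.

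**The case against.** The strongest reply is that the bullet names a regression family and stops. It does not say that robust errors are excluded. This is a condensed article, a full protocol is cited, and a variance estimator for a secondary end-point is often left to the analysis plan. That would settle the matter if the article were silent throughout. It is not: it states the variance method for the neighbouring count and omits it here. The contrast stands as an inconsistency, whether it is a drafting slip or a choice.

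The second reply also has force: nothing in the article demonstrates over-dispersion. Detection rates of 60–62% fit a pure Poisson count with mean 0.92–0.97. A reader might infer that the intervals are bound to be too narrow, or that a spurious finding of fewer adenomas is likely. The documents support neither. The inflation is conditional on a distribution they do not give. Even at a variance/mean ratio of 2.5, only about half of the 21.5% two-sided error, roughly 11% per comparison, would favour treatment.

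Three other tempting arguments should be left aside:

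- **Centre.** Leaving out centre is not a main source of optimism, because randomisation is stratified by centre.
- **The patient random intercept.** In the left/right model it does not show that the plan presupposes over-dispersion. It also serves to link two counts from one person, and that model is only tentative.
- **Protection of the wrong count.** One might say the plan guards the count that needs it less. The article gives no dispersion for either count, and the purpose it states for robust errors, in the primary analysis, is clustering by centre.

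**Conclusion.** The point holds as an unexplained inconsistency with a conditional consequence. As written, the total count would be analysed with standard errors that are valid only without over-dispersion. If participants' adenoma rates vary, the intervals would be too narrow. Under the negative binomial assumption with 60% affected, the true size of a 5% test runs from about 5% at mean 0.92 to 33% at mean 2.0. Where the trial falls in that range cannot be determined from the article.

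This should be fixed, but it does not endanger the trial. A reader might infer that a central result is at risk. However, the end-point is one of seven secondary end-points and the article does not call it key. The primary end-point is binary and already has robust errors. The power calculation does not use the count.

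**What to change.** Amend the bullet for total adenomas to specify Poisson regression with robust (sandwich) standard errors, matching the 'advanced' count. Alternatively, specify negative binomial regression. If a different variance method for the two counts is intended, give the reason. Settle the choice before unblinding, so that it cannot depend on the results.

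The cost is one line of text, with no extra patients or data. If there is over-dispersion, the intervals become wider. If there is none, almost nothing is lost: in the pure Poisson case with mean 0.92 the simulated size was 4.9% with robust errors and 4.8% with model-based errors.
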